## 6.2 Eligibility Criteria [10]

### 6.2.1 Inclusion criteria

Patients who meet the following criteria at the start of treatment are eligible for the study:

1. Adults (≥18 years)
2. Undergoing planned or unplanned (elective/expedited or emergent) cardiac surgery (bypass or valve), abdominal surgery (open or laparoscopic) or vascular surgery (open or hybrid) of the lower limb or major amputation (above and below knee)
3. Anaemia (Hb <130g/L in males and <120g/L) in females
4. Willing and able to undergo follow-up visits

6.2.2 Exclusion criteria
Patients who, at the start of treatment, meet any of the following criteria are not eligible for the study:

1. Blood transfusion at operation or blood transfusion in previous 3 months
2. Erythropoietin or intravenous iron in the previous 4 weeks
3. Known hypersensitivity to (ferric carboxymaltose or equivalent) or its excipients
4. Active infection on therapeutic antibiotics
5. Known chronic liver disease
6. Known other cause for anaemia (eg. untreated B12 or folate deficiency or myelodysplasia)
7. Known family history of haemochromatosis or TSATS >50%
8. Pregnancy or lactation
9. Unable to provide written informed consent

All patients will follow the standard care pathways and thresholds for anaemia management, typically red blood cell (RBC) transfusion for Hb <70g/L.

## 6.3 Recruitment [15]

This is a hospital-based study at sites in Australia and the United Kingdom. Participating hospital sites may enrol patients into one or more of the clinical cohorts. Further locations may be added. Patients will be identified through the normal clinical patient pathways for surgery and anaesthesia such as surgical outpatient and preoperative clinics, surgical admissions, or inpatient wards. **As part of normal clinical assessment for major surgery, all patients will be screened for anaemia. Following** **review and discussion with the treating** clinical **team, patients** will be invited to **participat**e **in the trial.**

# 7. Study Procedures [13]

7.1 Informed consent [26a][26b]

Written informed consent will be obtained prior to performing any trial-specific procedure by the investigator or delegate. Participants must be given written and verbal information, in lay terms, of the aims, methods, anticipated benefits and potential hazards, and given sufficient time to consider whether they wish to participate. The participants must be notified that participation is voluntary, and that they are free to discontinue treatment or withdraw consent from the study at any time without any disadvantages for their future care and treatment. If the participant agrees to participate in the trial, they will be asked to initial, sign and date the latest version of the Participant Information Consent Form (PICF). The Investigator or delegate will then sign and date the form. A copy of the PICF will be given to the participant, a copy will be filed in the medical notes.

Patients will be invited at the time of study enrolment to provide optional written informed consent for donation of blood sample for future biological or translational sub-studies
for future research use, pending relevant ethics and governance approval.

## 7.2 Randomisation procedures

### 7.2.1 Allocation [16a] [16b] [16c]

Random allocation will be performed using a computer-generated code, access via a web-based service. Randomisation will be performed by the unblinded study personnel delegated this responsibility by the principal investigator as evidenced by documentation in the delegation log. The blinded staff will not have access to the randomisation system and will therefore remain blinded to the treatment allocated. Each unblinded study personnel will be trained in the use of the web-based service before they are provided with their own individual password and pin code to access the service.

### 7.2.2 Blinding [17a]

As active and placebo fluids cannot be matched in appearance, unblinded study personnel (unblinded nurse or hospital pharmacist) will be responsible for the preparation of the study drug. The study drug will be shielded from vision (light protection bags) and administered through black tubing. The unblinded study personnel will also dispose of the administration kit in a concealed way.

### 7.2.3 Unblinding [17b]

Treatment unblinding will only occur when there are legitimate clinical concerns where the appropriate management of the participant necessitates knowledge of the treatment allocation. All cases of emergency unblinding will be thoroughly documented and reported to the data safety monitoring board (DSMB). After all participants have completed the study, participants will be notified which arm of the study they took part in.

## 7.3 Perioperative group

| **Perioperative group** | | | | | | | | | |
| --- | --- | --- | --- | --- | --- | --- | --- | --- | --- |
| **Perioperative group (Amputation)** | | | | |  | | | | |
| **Procedures** | **Pre Op (- 4 weeks to 0 day)** | **Baseline Day of surgery** | **Post Op Days 1,2,4** | **Discharge or day 8** | **2 weeks (± 3 days)** | **4 weeks (± 1 wks)** | **8 weeks (± 2 wks)** | **12 weeks (± 2 wks)** | **16 weeks (± 2 wks)** |
| **Informed consent** | X |  |  |  |  |  |  |  |  |
| **Inclusion/ exclusion criteria** | X |  |  |  |  |  |  |  |  |
| **Medical History** | x |  |  |  |  |  |  |  |  |
| **Concomitant medications** | x |  |  | x | x | x | x | x | x |
| **Clinical frailty scale** | x |  |  | x | x | x | x | x | x |
| **Routine clinical**  **blood tests** | x |  | x | x | x | x | x | x | x |
| **Core Laboratory assessments** |  | x | x | x | x | x | x | x | x |
| **Randomisation** |  | x |  |  |  |  |  |  |  |
| **Study medication administration** |  | x |  |  |  |  |  |  |  |
| **Adverse events** |  | x | x | x | x | x | x | x | x |
| **Quality of Life assessments** |  |  |  | X | x | x | x | x | x |
| **Functional assessments** |  |  |  | x | x | x | x | x | x |

**7.3.1 Schedule of assessments**

**7.3.2 Study Visits**

Patient assessments will start on admission to hospital on the day of surgery (Day 0). Patients will be randomly assigned to receive either intravenous iron or placebo at skin closure in operating theatres administered by the anaesthetics team, if this is not possible for logistical reasons, the patient will receive the one-off infusion in recovery as per local policy.

During inpatient admission, results from routine blood tests measured at day 1, 2, 4 and 8 (if still an inpatient at this time) will be recorded on the CRF. These will be performed as part of the routine clinical post-operative care. An additional SST blood sample (6-8mL or 1.5 teaspoons) will be collected at the time of the routine blood draws for core laboratory analysis.

Subsequent follow up in outpatient at weeks 2, 4 (+/- 1), 8 (+/- 2), 12 (+/- 2), 16 (+/- 2) from the operation date. Functional and quality of life assessments will be collected at those time points.

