**Methods**

AMBLE will be a prospective, parallel-group, double blinded, 2 by 2 factorial, randomised, multi-centre trial designed to investigate iron deficiency in cardiac, abdominal, and vascular surgery patients. Potential participants will be identified through normal clinical pathways for surgery and anaesthesia such as surgical outpatient and preoperative clinics, surgical admissions, or inpatient wards. The Perioperative group will assess the mechanisms of iron deficiency and response to intravenous iron therapy in the perioperative period. The Recovery group will assess feasibility to test patients physical and quality of life recovery in the postoperative setting and assess if this differs between iron deficient and iron replete patients.

Two separate groups of patients will be assessed:

- The Perioperative group of patients included if about to undergo major cardiac, abdominal and vascular surgery to assess the mechanisms of iron deficiency in the perioperative period.
- The Recovery group of patients included 4 weeks after hospital discharge following major cardiac, abdominal and vascular surgery to assess recovery of physical function and anaemia.

Following screening, participants who provide informed consent will undergo baseline blood tests, quality of life (QoL) questionnaires and functional assessments. Following this, participants will be randomised to either an intravenous iron administered either directly post-operatively in the Perioperative group or 4 weeks post operatively in the Recovery group, or placebo.

Follow up assessments will occur:

- The Perioperative group at Days 1, 2, 4, 8 and 2 weeks then weeks 4, 8, 12 and 16.
- The Recovery group weeks 4, 8, 12 and 16.

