## 7.4 Recovery group

**7.4.1 Schedule of assessments**

| **Procedures** | **Baseline**  **(4 weeks post discharge)** | **4 weeks (± 1 wks)** | **8 weeks (± 2 wks)** | **12 weeks (± 2 wks)** | **16 weeks (± 2 wks)** |
| --- | --- | --- | --- | --- | --- |
| **Informed consent** | x |  |  |  |  |
| **Inclusion/ exclusion criteria** | x |  |  |  |  |
| **Medical History** | x |  |  |  |  |
| **Concomitant medications** | x |  |  |  |  |
| **Clinical frailty scale** | x | x | x | x | x |
| **Routine clinical**  **blood tests** | x | x | x | x | x |
| **Core Laboratory assessments** |  | x | x | x | x |
| **Randomisation** |  | x |  |  |  |
| **Study medication administration** |  | x |  |  |  |
| **Adverse events** |  | x | x | x | x |
| **Quality of Life assessments** | x | x | x | x | x |
| **Functional assessments** | x | x | x | x | x |

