### 11.1.1 Primary Endpoint Change in Hb concentration from baseline to 90 days following randomisation

### 11.1.2 Secondary Endpoints Laboratory:

1. Change in Routine Iron markers
2. Changes in Experimental Iron markers
3. Changes in proteomic and metabolomic profiles.
4. Mental and physical recovery after surgery
5. Complication rate at 30 days post operation
6. Length of hospital stay
7. Re-operations
8. Unplanned re-admission to hospital for complications
9. Days Alive and at Home (DAH) 30 & 90
10. Change in clinical frailty score and activities of daily living (Nottingham extended ADL scale)
11. Changes in Sarcopenia
12. Changes in functional assessments
13. Changes in Quality of life

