## 11.4 Statistical Analysis [20a]

Analyses will be based on all randomised participants. Reporting of research findings will be in accordance with CONSORT guidelines. Baseline demographic data and other participant characteristics will be expressed as means and standard deviations for continuous variables and counts and percentages for categorical variables, with 95% confidence intervals provided for estimates of interest where appropriate. The differences in baseline characteristics will be evaluated by either $\chi^{2}$ or Fisher extract test for categorical variables and an independent samples t-test for continuous variables. Changes in recovery outcome scores will be compared for each participant as the difference between baseline and each specified time points scores with univariate analyses comparing changes in outcome.

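### The Perioperative schedule has no pre-treatment quality of life or functional assessment, although the protocol promises one and analyses change from baseline

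*Protocol*

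**What the plan says.** The abstract (Methods) says that "participants who provide informed consent will undergo baseline blood tests, quality of life (QoL) questionnaires and functional assessments", and it places randomisation after these. It makes no exception for either group.

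The Perioperative schedule table in section 7.3 has two columns before treatment takes effect: a pre-operative column (4 weeks before surgery to day 0) and a day-of-surgery baseline column. The functional row reads "Functional assessments | | | | x | x | x | x | x | x". Its first three cells (pre-operative, day of surgery, post-operative days 1, 2 and 4) are blank, and the first mark is at discharge or day 8. The quality of life row has the same pattern. Section 7.3.2 lists the outpatient visits at weeks 2, 4, 8, 12 and 16 and adds "Functional and quality of life assessments will be collected at those time points". It names no pre-operative assessment of either kind.

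On the analysis side, section 11.1.2 lists "Changes in functional assessments" and, separately, changes in quality of life. Section 11.4 states: "Changes in recovery outcome scores will be compared for each participant as the difference between baseline and each specified time points scores".

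For the Recovery group, the table in section 7.4.1 marks quality of life, function, frailty and routine bloods at baseline, but the core-laboratory row reads "Core Laboratory assessments | | x | x | x | x", with a blank at baseline. Randomisation and study medication are marked in the 4-week column. Section 7.4.2 instead says that randomisation follows the baseline assessment.

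**The concern.** A change score needs a value from before treatment. In the Perioperative group, study drug is given at skin closure or in the recovery area (section 7.3.2), so discharge or day 8 comes after both the operation and the infusion. A site that follows the table will not collect the value that the analysis section subtracts, and no later analysis plan can recover a measurement that was never made.

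The obvious workaround is to treat the first available score as baseline. That creates two problems. A score taken after randomisation may already carry a treatment effect, and subtracting it removes part of what the trial is trying to estimate. It also changes the meaning of recovery: change would be measured from an early post-operative state and not from the patient's condition before surgery.

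The Recovery core-laboratory question is similar but depends on when dosing takes place. Section 11.1.2 lists changes in experimental iron markers and in proteomic and metabolomic profiles, and section 7.2 (core laboratory assessments) shows that markers such as erythropoietin, erythroferrone and hepcidin come from the core sample.

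**Working it through.** **Step 1. The protocol's own number.** Section 11.2 gives 2 groups × 3 surgical cohorts × 2 arms × 20 = 240, which matches the stated total. The Perioperative group is 3 × 40 = 120, or 60 per arm. There is no formal sample size calculation, so there is no power figure to reproduce.

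**Step 2. Marks before study drug, row by row (section 7.3 table).**

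- Quality of life: none. First mark at discharge or day 8.
- Functional assessments: none. First mark at discharge or day 8.
- Clinical frailty scale: one, in the pre-operative column.
- Routine blood tests: "blood tests | x | | x | x | x | x | x | x | x", so one in the pre-operative column, none in the day-of-surgery column, and further marks from day 1.
- Core laboratory: a mark in the day-of-surgery column.

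Frailty and routine bloods do carry a pre-operative mark, so the blanks are specific to quality of life and function. Section 7.3.2 independently gives only post-operative times for them. Planned Perioperative patients with a scheduled pre-treatment score: 0 of 120.

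**Step 3. What a day-8 baseline would do.** Let d8 and d12 be the true between-arm differences at day 8 and week 12. The between-arm difference in change from day 8 to week 12 has expectation d12 − d8. It equals the week-12 effect only if d8 = 0, which the protocol neither states nor can check.

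**Step 4. What the missing baseline costs in precision (illustration).** Assume 60 per arm, two-sided 5%, 80% power, and a correlation r between baseline and follow-up. The protocol gives no r, so a range is shown. The detectable standardised difference is:

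- follow-up score alone: (1.960 + 0.842) × √(2/60) = 0.51 SD;
- adjusted for baseline: 0.511 × √(1 − r²), giving 0.49, 0.44 and 0.37 SD at r = 0.3, 0.5 and 0.7;
- simple change score, as in section 11.4: 0.511 × √(2(1 − r)), giving 0.61, 0.51 and 0.40 SD at the same r.

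A pre-treatment score therefore helps most when used as a covariate. A simple change score gains nothing over the follow-up score at r = 0.5 and is worse below it. Within one surgical cohort (20 per arm) the follow-up score alone detects 0.89 SD, against 0.77 SD adjusted at r = 0.5.

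**Step 5. Recovery core sample.** Two readings are possible.

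- Dosing follows the baseline visit (section 7.4.2): the first scheduled core sample is 4 weeks later, so no pre-dose sample exists.
- Dosing is at the 4-week column (section 7.4.1): a core sample falls at that visit, but nothing says that it is drawn before the dose.

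Neither reading guarantees a pre-dose value.

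**The case against.** Several points can fairly be made on the other side.

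- *The intention is stated.* The abstract commits to baseline quality of life and functional assessments, so this is a contradiction more than a deliberate omission. That is correct. But sites work from the schedule and visit text, and both leave the assessments out. The statement that section 7.3.2 assessments start on the day of surgery does not help, because the two cells in that column are blank.
- *The arms can be compared on follow-up scores alone.* They can, and randomisation makes that comparison valid. It is not the analysis that section 11.4 describes, and it gives up the precision shown in step 4.
- *Quality of life and function matter mainly in the Recovery group.* The protocol calls the Perioperative group mechanistic, and the Recovery baselines for these outcomes are scheduled. This limits the damage. However, section 11.1.2 does not restrict the change endpoints to one group, and section 11.4 refers to each participant.
- *The table carries an unexplained amputation sub-header.* Its reach to all 120 patients is therefore not wholly certain. It is the only Perioperative schedule shown, and section 7.3.2 agrees with it.

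Two stronger readings are tempting and are not supported. A reader might infer from the blank day-of-surgery cell that the primary endpoint, "Change in Hb concentration from baseline to 90 days following randomisation", has no Perioperative baseline. It has one: routine bloods are scheduled pre-operatively, up to 4 weeks before surgery and possibly on day 0. An older value taken before randomisation may cost some precision but does not bias the comparison. Which haemoglobin counts as baseline is a clarification only. A reader might also infer that no Recovery patient would have a pre-dose core sample. That takes the sampling time from the table and the dosing time from the text. On the table's own terms, a sample falls at the dosing visit.

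**Conclusion.** The point holds for Perioperative quality of life and function. If the schedule is followed literally, 0 of 120 planned patients have a pre-treatment score, in contradiction to the abstract, and the change analysis in sections 11.1.2 and 11.4 cannot be formed without a post-randomisation baseline. This rests on taking the section 7.3 table as applying to the whole Perioperative group. The precision figures are illustrations under assumed correlations. They are not protocol quantities.

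The Recovery core-laboratory gap is secondary: a conflict between sections 7.4.1 and 7.4.2 under which a pre-dose sample is not guaranteed, though it is not shown to be absent. The primary endpoint remains computable.

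**What to change.** 1. Mark quality of life and functional assessments in the pre-operative column of the Perioperative table, and say so in section 7.3.2, so that both agree with the abstract.
2. State in section 11.4 that no value obtained after study drug serves as baseline for any change endpoint.
3. Reconcile sections 7.4.1 and 7.4.2 on when Recovery patients are randomised and dosed. Whichever is intended, schedule the first core-laboratory tube explicitly before the dose.
4. As a clarification, name which pre-operative haemoglobin is the baseline if several exist.

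The cost is a protocol amendment, some extra time at a pre-operative contact that already exists, and, depending on how item 3 is resolved, one more tube at the Recovery baseline blood draw. Some emergency patients will not manage functional tests before surgery. Their baselines will be missing and should be reported as such, not replaced by a post-operative score. If the assessments cannot be added, the honest alternative is to reword the Perioperative endpoints as between-arm comparisons of follow-up scores and to accept the lower precision.

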## 7.4 Recovery group

**7.4.1 Schedule of assessments**

| **Procedures** | **Baseline**  **(4 weeks post discharge)** | **4 weeks (± 1 wks)** | **8 weeks (± 2 wks)** | **12 weeks (± 2 wks)** | **16 weeks (± 2 wks)** |
| --- | --- | --- | --- | --- | --- |
| **Informed consent** | x |  |  |  |  |
| **Inclusion/ exclusion criteria** | x |  |  |  |  |
| **Medical History** | x |  |  |  |  |
| **Concomitant medications** | x |  |  |  |  |
| **Clinical frailty scale** | x | x | x | x | x |
| **Routine clinical**  **blood tests** | x | x | x | x | x |
| **Core Laboratory assessments** |  | x | x | x | x |
| **Randomisation** |  | x |  |  |  |
| **Study medication administration** |  | x |  |  |  |
| **Adverse events** |  | x | x | x | x |
| **Quality of Life assessments** | x | x | x | x | x |
| **Functional assessments** | x | x | x | x | x |

**7.4.2 Study Visits**

Patient assessment will start four weeks post discharge from hospital. Following baseline assessment, patients will be randomly assigned to receive either intravenous iron or placebo in the outpatient setting.

Participants will be required to attend up to 4 occasions for functional, quality of life assessment, and blood sampling. Where possible these visits will coincide with normal clinical follow up after discharge from hospital and it is envisaged only two additional visits will fall outside routine clinical care. The blood tests, QoL questionnaires and functional assessments will be undertaken at the same clinic visit.

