# 5. Trial Design [8]

Multicentre, prospective, parallel-group, double blinded, 2 by 2 factorial, randomised controlled trial comparing intravenous iron or placebo administration in anaemic patients undergoing major cardiac, abdominal, or vascular surgery.

Perioperative group: Intravenous iron or placebo will be administered immediately post-operatively.
Recovery group: Intravenous iron or placebo will be administered 4 weeks post-operatively.

All patients will be followed for 16 weeks from date of randomisation.

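### Recovery group: the schedule table and the text disagree on when patients are randomised and dosed, which moves the visits by about four weeks relative to the 90-day endpoint

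*Protocol*

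**What the plan says.** The places that bear on Recovery timing, all in the Protocol:

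- **Section 7.4.2 (Study Visits, Recovery).** "Patient assessment will start four weeks post discharge from hospital", and then "Following baseline assessment, patients will be randomly assigned to receive either intravenous iron or placebo in the outpatient setting". No separate, later dosing visit is described.
- **Section 7.4.1 (Recovery schedule).** The first column is baseline, set four weeks after discharge. Visits follow at 4, 8, 12 and 16 weeks. The baseline cell is empty for randomisation ("Randomisation | | x") and for treatment ("Study medication administration | | x"). Core-laboratory samples and adverse events also start in the 4-week column. Routine bloods, which supply the haemoglobin, are marked at every visit including baseline: "blood tests | x | x | x | x | x".
- **Section 5 (Trial Design).** "Recovery group: Intravenous iron or placebo will be administered 4 weeks post-operatively". Also: "All patients will be followed for 16 weeks from date of randomisation".
- **Abstract (Methods) and Section 6 (Study Population).** Both describe Recovery patients as entering four weeks after discharge. The Abstract also gives dosing as four weeks after surgery.
- **Section 11.1.1 (Primary Endpoint).** "Change in Hb concentration from baseline to 90 days following randomisation".

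**The concern.** The primary endpoint and the length of follow-up are both counted from randomisation. In the Recovery group, the place of randomisation on the visit calendar depends on which section a site follows. The table puts it one visit after baseline, the visit text puts it after the baseline assessment with no further visit named, and Section 5 dates treatment from the operation rather than from discharge.

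This matters in three ways:

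- **Endpoint time.** The same labelled visit falls about four weeks apart in time since treatment, so the visit nearest day 90 changes.
- **Baseline.** The haemoglobin in the baseline column is either taken at about the time of dosing or several weeks before it, when it may still be changing after surgery.
- **Data capture.** If sites dose at the baseline visit, the table schedules neither a core-laboratory sample nor an adverse-event record there. Analysis can re-time visits from the recorded randomisation date, but it cannot recover a pre-dose sample that was never drawn. Section 11.1.2 lists changes in experimental iron markers as an endpoint.

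**Working it through.** **Inputs**

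- Visit weeks and windows (Section 7.4.1): 4 ± 1, 8 ± 2, 12 ± 2, 16 ± 2.
- Endpoint: 90 days after randomisation (Section 11.1.1).
- Follow-up: 16 weeks, or 16 × 7 = 112 days, from randomisation (Section 5).
- Numbers (Section 11.2): Recovery is 3 cohorts × 2 arms × 20 = 120. Both groups together are 2 × 120 = 240, which agrees with the stated total.
- Assumption: visit weeks are counted from the baseline column.

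**Text reading: randomised at baseline.** For a visit at week w with half-window h, days since randomisation are 7w, with range 7(w − h) to 7(w + h).

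**Table reading: randomised at the 4-week visit, which may itself fall at week 3 to 5.** Days since randomisation are 7(w − 4), with range 7(w − h − 5) to 7(w + h − 3).

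| Visit | Text reading: day (range) | Table reading: day (range) |
| --- | --- | --- |
| Week 8 | 56 (42 to 70) | 28 (7 to 49) |
| Week 12 | 84 (70 to 98) | 56 (35 to 77) |
| Week 16 | 112 (98 to 126) | 84 (63 to 105) |

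For example, week 12 on the table reading is 7 × (12 − 4) = 56, with range 7 × (12 − 2 − 5) = 35 to 7 × (12 + 2 − 3) = 77.

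**Against the 90-day endpoint.** On the text reading, day 90 lies in the week-12 window (70 to 98) and in no other. On the table reading, the week-12 window (35 to 77) excludes it and the week-16 window (63 to 105) includes it. Counted from baseline, day 90 after randomisation is study day 90 + 28 = 118 (range 90 + 21 = 111 to 90 + 35 = 125). The last visit is nominally at study day 112 (98 to 126), so it falls 118 − 112 = 6 days short at nominal times.

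**Against 16 weeks of follow-up.** The text reading gives 112 days, as stated. The table reading gives 16 − 4 = 12 weeks nominally. Sixteen weeks from randomisation would then be study week 20 (19 to 21), for which no visit is scheduled.

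**Baseline haemoglobin.** On the table reading, the baseline-column value precedes dosing by 4 weeks (3 to 5). Routine bloods are also marked at the 4-week visit, so a value nearer dosing would exist, but the protocol does not say which one is the baseline.

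**Dosing-visit records.** On the table reading, the dosing column carries a core-laboratory mark and an adverse-event mark. On the text reading, the dosing column carries neither.

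**The case against.** The strongest reply is that this is a clerical slip. In the Perioperative schedule (Section 7.3), the same four rows (core laboratory, randomisation, study medication, adverse events) also begin in the second column, which there is the day of surgery. The Recovery table may be that template with the column relabelled. That is plausible, but the document does not settle it. The four marks form a coherent block that a site could follow as written. The limit of four attendances in Section 7.4.2 does not settle it either, since the table has five visit columns.

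It can also be said that randomisation following the baseline assessment fixes an order rather than a day, so that sentence alone does not contradict the table. This is fair. But Section 7.4.2 names no second visit for dosing, and the table, counted from baseline, conflicts with the 16 weeks in Section 5.

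A reader might infer more than the documents support:

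- **That day 90 cannot be reached.** It can. Even on the table reading, the last-visit window (63 to 105) contains it.
- **That the endpoint has no time zero.** Section 11.1.1 names randomisation. Only its place in the Recovery calendar is in conflict. Perioperative table and text agree on the day of surgery.
- **That the lack of a visit on exactly day 90 is a defect.** A 12-week visit with a two-week window covers day 90 when counted from randomisation.
- **That the treatment comparison is biased, or that the two groups become non-comparable.** The shift applies to both arms alike. The groups are described as separate, and the analysis section specifies no comparison between them.
- **That adverse events at dosing would go unrecorded.** Section 7.5 (discontinuing or modifying interventions) and Section 9.1 require recording, so only the schedule mark is absent.

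**Conclusion.** The point stands, confined to the Recovery group: 120 of 240 planned patients. The protocol gives conflicting times for randomisation and dosing, and the difference between table and text is 4 weeks (3 to 5).

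- If the table is followed, the visit nearest the endpoint becomes week 16 rather than week 12, nominal follow-up after randomisation is 12 weeks rather than 16, and the baseline-column haemoglobin is taken 3 to 5 weeks before dosing.
- If the text is followed, endpoint time and follow-up length are in order, but no core-laboratory sample or adverse-event record is scheduled at the dosing visit.
- Separately, dating dosing from surgery and dating entry from discharge differ by the length of the hospital stay, which the protocol does not give for its own patients.

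The consequence is a blurred endpoint time and possible loss of pre-dose data, more so if sites follow different sections. It is not a bias of iron against placebo. The day counts assume that visit weeks run from the baseline column. The contradiction itself needs no assumption.

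**What to change.** The sponsor should reconcile the Abstract (Methods) and Sections 5, 6, 7.4.1 and 7.4.2 on when Recovery patients are randomised and dosed. No timing is proposed here. Once that is confirmed:

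1. Correct the Recovery table so that visit weeks are counted from randomisation, as Sections 5 and 11.1.1 require.
2. State which haemoglobin is the pre-dose baseline, and which visit and window serve the 90-day endpoint.
3. Mark a pre-dose core-laboratory sample and adverse-event recording at the dosing visit.

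The cost is an amendment to one table and a few sentences. If the table's timing is the one confirmed, 16 weeks from randomisation may need a later last visit, at about week 20 from the present baseline.
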